## Abstract

**Background:**

Severe mental disorders like psychotic disorders including schizophrenia and schizoaffective disorders have a 12-month-prevalence of 2.6, bipolar disorders of 1.5 % in Germany. The relapse risk is high; so many patients need intensive monitoring and lifelong treatment. A high medication adherence is essential for a successful treatment. But in practice, medication adherence is low and decreases over time. Telemedical care concepts might improve treatment and bridge gaps between in- and outpatient treatment.

A telemedical care concept based on regular telephone calls and short text messages was developed. The primary objective is to assess whether regular telephone calls and text messages can improve the medication adherence of patients. Secondary objectives are the reduction of rehospitalization rates, the improvement of quality of life and of the severity of symptoms.

**Methods/design:**

The Tecla study (Post stationary telemedical care of patients with severe psychiatric disorders) is a two-armed prospective randomized controlled trial. The participants in the intervention group receive in addition to usual care regular telephone calls every 2 weeks and weekly text messages on patient-individual topics during a 6 months period. Patients in the control group receive only regular care. Inclusion criteria are a physician-diagnosed bipolar disorder, schizoaffective disorder or schizophrenia and a signed informed consent. Exclusion criteria are planned inpatient treatments within the next 6 months and being non-reachable by phone. After 3 and 6 months both groups receive follow up assessments.

**Discussion:**

The primary objective of this study is the medication adherence that is measured with the Medication Adherence Report Scale, German version (MARS-D). The MARS-D is a self-report with five items. Adherent behaviour is mostly overestimated using self-reports. The strength of the MARS-D is to detect non-adherent behaviour. The original Medication Adherence Report Scale in English language (MARS-5) was developed to encourage the patient to answer truthfully to the questions that are asked in a non-threatening and non-judgmental way to minimize social desirability bias in admitting non-adherent behaviour.

**Trial registration:**

This study is registered at 2015\05\21at the German Clinical Trials Register DRKS00008548.

## Background

### Epidemiology

Nineteen new schizophrenia-cases per 100,000 people per year are diagnosed in Germany [1]. Prevalence rates of mental disorders are high all over the world, also in Europe and Germany. The lifetime prevalence of schizophrenia worldwide is estimated as 1 % of the population. The 12-month-prevalence of schizophrenia and other psychotic disorders in the German population is about 2.6 %; the 12-month-prevalence of bipolar disorders about 1.5 % [2]. In Germany 2 to 4 % of the total health care costs are caused by schizophrenic disorders [1]. Mental disorders are associated with a high disease burden. People with current mental disorders have three times as much days of limitation than people without any mental disorder [2]. Worldwide, schizophrenia is one of the ten diseases with the highest number of years of life lived with disability (YLD) [1]. This also leads to high social costs [3] because mental disorders are the most common cause for early retirement, work losses and reduced work productivity [4]. The restricted participation in social and professional life often causes a severe reduction of quality of life [1].

### Utilization and adherence

Treatment rates of mental disorders in general are low. The Study of Health in Pomerania (SHIP) [5] revealed a treatment rate for mental disorders of 20 % [6]. In the Mental Health Supplement of the German National Health Interview and Examination Survey (GHS-MHS) treatment rates for psychotic disorders (including schizophrenia) of 30.3 % of the cases and of 82.4 % for highly co-morbid cases were found. Patients with bipolar disorders received treatment in 42.2 % of the cases (62.4 % treatment in highly co-morbid cases) [7].

The diagnosis of schizophrenia implies in most cases a lifelong medical treatment. In the acute stages of schizophrenia, therapy is applied in the hospital. In this stage, drug therapy is essential to achieve a rapid and effective reduction of acute psychotic symptoms. After discharge from the hospital, adherence to medication is essential to avoid relapses. However, non-adherence is one of the major problems in patients with schizophrenia [8]. The proportion of adherent patients is 35–50 % in patients with schizophrenia and bipolar disorders [9–11]. In the outpatient setting, the adherence of patients taking atypical antipsychotics drops to 55 % after 12 months [12]. Non-adherence is associated with a higher risk of psychiatric hospitalizations [13]. Without drug therapy the relapse rate is about 70 % in the first year and about 80 % in the second year after starting drug treatment [14–16]. With drug therapy the recurrence rate is significantly lower: about 30 % in the first year and about 50 % in the second year [1].

In total 93 % of the patients with schizophrenia in Germany are treated in outpatient psychotherapeutic facilities (e.g. practices, psychiatric walk-in clinics or day-care). Especially in rural regions, waiting lists are long. A survey among practicing psychotherapists in Germany showed that adult patients have to wait on average 1.9 months for an initial interview and 4.6 months for psychotherapy [17].

### Telemedical care

Telemedical concepts have a potential to support the treatment of psychiatric patients and to provide new options in patient care. Several studies have evaluated the possibilities and limitations of telemedical care in the treatment of patients with schizophrenia. Salzer et al. [18] conducted a study with *n* = 32 schizophrenic patients consisting of brief weekly telephone-based interviews. The results showed that telephone interventions are acceptable and feasible. Because of the small study sample, these results were seen as preliminary data.

Leach and Christensen performed a systematic review about telephone-based interventions for patients with mental disorders (six in the area of depression, three of anxiety, three of eating disorders, one of substance abuse and one of schizophrenia). Although the included studies all had small simple sizes, they showed positive results [19].

Alvarez-Jimenez et al. conducted a systematic review examining the usability, acceptability, feasibility, safety or efficacy of user-led, internet- or mobile-based interventions with patients of the schizophrenia-disorders spectrum. Twelve studies were included. Patients mainly used the internet and mobile phone based interventions. The authors conclude that online, social media and mobile technologies were acceptable and feasible for patients [20].

Kasckow et al. summarized a systematic review including 18 studies with telephone-based, internet-based or video-based telehealth systems for patients with schizophrenia, that telephone, internet and video-interventions appears to be feasible [21].

Improving medication adherence using telemedical methods was discussed in several studies. In 2008 a randomized controlled trial was published that examined telephone intervention problem solving (TIPS) for patients with schizophrenia [22]. These telephone interventions were initiated weekly by telenurses and improved significantly the patient’s adherence to their psychiatric medication. Adherence was measured by pill counting and record review. The participants in the intervention showed an adherence of on average 80 %, while in control participants this rate was 60 %.

A study in Spain examined a telephone based strategy to improve adherence to antipsychotic treatment in schizophrenia. Nine hundred twenty-eight patients received a monthly telephone call by a nurse to assess therapeutic adherence and subjective attitude towards medication over a period of 4 months. Being adherent was defined as the intake of at least 60 % of the prescribed medication dose. Patients in the intervention group (*n* = 410) were significantly more adherent (OR = 3.3 95 % CI 1.6–6.6, *P* = 0.0001) than patients in the control group (*n* = 402) [23].

The study Mobile Assessment and Treatment for Schizophrenia (MATS) with 55 participating patients examined the use of mobile phone text messaging. 6 days a week individualized text messages were sent to the participants addressing the topics medication adherence, social activities and auditory hallucinations during the 12-week-intervention-period. Participants who were living independently achieved a significant improvement in medication adherence and benefited more than participants living in assisted living facilities. This is probably due to the fact, that the participants in assisted living facilities already have support and assistance in taking medications. This study was a pilot study without a control group [24].

Summarized, first studies with telemedicine concepts for patients with schizophrenia show positive results. However, evidence based on methodically sound studies with a sufficient number of participants is still limited.

The intention of Tecla study (Post stationary telemedical care of patients with severe psychiatric disorders) is to improve medical care for patients with severe mental disorders in Western-Pomerania/Germany using a telemedical intervention concept on the basis of regular, individualized telephone calls and text-messages.

## Methods/design

### The Tecla study

The outlined study Tecla is designed according to the SPIRIT Guidelines [25]. Tecla is a cooperation between the Institute for Community Medicine and the Department of Psychiatry and Psychotherapy, both University Medicine Greifswald, and the Bethanien Hospital for Psychiatry, Psychosomatics and Psychotherapy Greifswald gGmbH. An Integrated Telemedicine Centre is affiliated to the Institute for Community Medicine [26–28].

The study region Western-Pomerania is located in the very northeast of Germany in the federal state of Mecklenburg-Western Pomerania. It is a sparsely populated rural region with 460,000 inhabitants. Both in- and outpatient psychiatric and psychotherapeutic facilities and walk-in clinics are mostly located in the larger towns of the region.

### Research objectives

Primary objective of the Tecla Study is a better medication adherence after 6 months of additional telemedical treatment in the intervention group compared to a control group receiving usual care.

Secondary outcomes are a lower proportion of rehospitalized participants after 6 months, a longer time without unplanned rehospitalization, an improvement in quality of life and an improvement in the severity of the psychopathology.

Additionally, the acceptance of the telephone and text message interventions by the participants will be evaluated in the intervention group.

### Study design

The Tecla study is a controlled randomized prospective intervention study. Participants are recruited shortly before their discharge from the psychiatric hospital after inpatient or combined inpatient/outpatient treatment. All participants receive a comprehensive baseline interview with a study-psychologist. After the baseline interview the participants are assigned at random to the intervention or control group. Participants in the intervention group receive phone calls every 2 weeks conducted by specially trained nurses as well as weekly individualized text messages additional to usual care. The duration of the intervention period is 6 months. The participants in the control group receive usual care. After baseline, a first follow-up assessment is conducted after 3 months. The final follow-up is conducted after 6 months. Both follow ups are conducted by telephone. The structure of the study is shown in a flow chart in Fig. 1.

**Fig. 1 Fig1:**
[figure not shown]
Flow chart of the study

### Power/sample size

The sample size estimate was based on the medication adherence, measured as a score with the questionnaire MARS-D. Given an adherent behaviour in the intervention group of 80 % (corresponding to a mean score of 19) and a lower adherent behaviour in the control group of 60 % (corresponding to a mean score of 15) after 6 months, a total sample size of 128 is needed (standard deviation 8.0 for both, alpha = 0.05, power = 0.80). Assuming a lost to follow up about 50 %, we will include 190 patients to the study.

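### The planned enrolment of 190 does not allow for the assumed 50 % loss to follow-up: about 95 completers would remain, with about 67 % power instead of the stated 80 %

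*Protocol article*

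**What the plan says.** The section Power/sample size of the protocol article bases the calculation on the MARS-D score at 6 months. It assumes a mean of 19 in the intervention group and 15 in the control group, with "standard deviation 8.0 for both, alpha = 0.05, power = 0.80". From these inputs it concludes that "a total sample size of 128 is needed".

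The next sentence moves from that number to enrolment: "Assuming a lost to follow up about 50 %, we will include 190 patients to the study".

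The time point agrees with the section Research objectives, where the primary aim is "better medication adherence after 6 months of additional telemedical treatment". The Discussion treats loss to follow-up as a real difficulty in this population. It warns that drop-out may be selective and that follow-up will be hard to obtain in the control group in particular.

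**The concern.** The required number, the assumed loss and the enrolled number stand in two consecutive sentences, and they cannot all be right. If 128 patients must be analysed and half of those enrolled are lost, enrolment must be twice 128. The stated 190 is only about one and a half times 128.

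This is the article's only justification of the sample size for the primary outcome. If the loss really is about one half, the trial has clearly less power than the article tells its readers. A null result would then be read as coming from a trial with a 20 % chance of missing the planned effect, when that chance is about one in three.

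**Working it through.** **Inputs, all from Power/sample size unless noted**

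- Means 19 and 15, so the difference is 4
- SD 8.0 in both arms, so d = 4 / 8 = 0.5
- Alpha 0.05, power 0.80
- Required total 128, assumed loss about 50 %, enrolled 190
- Two randomised arms (section Study design)

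The article states neither the sidedness of the test nor the allocation ratio. I assume a two-sided test and 1:1 allocation, because these reproduce the plan's figure.

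**Step 1: reproduce the 128.** A two-sided two-sample t-test with d = 0.5, alpha 0.05 and power 0.80 needs 63.77 per arm. This rounds up to 64 per arm, or 128 in total, with power 80.1 %. The match is exact. Alternatives fit less well:

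- The normal approximation gives 63 per arm, 126 in total.
- A one-sided test by the same approximation gives 100 in total.
- A comparison of the proportions 80 % and 60 % gives 164, or 182 with continuity correction.

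So 128 is the number of patients with a 6-month score that the test needs, before any allowance for loss.

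**Step 2: allow for the loss.** The number to enrol is N / (1 − loss):

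- 128 / (1 − 0.5) = 256
- Shortfall of the stated enrolment: 256 − 190 = 66
- For comparison, 128 × (1 + 0.5) = 192, close to the stated 190
- Loss at which 190 still yields 128: 1 − 128 / 190 = 0.326, or 32.6 %

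**Step 3: power with 190 enrolled.** The same t-test with 190 × (1 − loss) completers, split equally, gives:

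| Loss | Completers | Power |
|---|---|---|
| 30 % | 133 | 81.6 % |
| 32.6 % | 128 | 80.1 % |
| 35 % | 123.5 | 78.7 % |
| 40 % | 114 | 75.4 % |
| 45 % | 104.5 | 71.6 % |
| 50 % | 95 | 67.4 % |
| 55 % | 85.5 | 62.7 % |

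At 50 % loss the normal approximation gives 68.3 %, so the result does not depend on the choice of formula.

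**Step 4: what 95 completers can detect.** With 47.5 per arm, 80 % power requires d = 0.581, and 0.581 × 8 = 4.65 points. The planned difference is 4.

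**Step 5: unequal loss (my assumption; the article gives no split).** With 40 % loss in the intervention arm and 60 % in the control arm, 95 × 0.6 = 57 and 95 × 0.4 = 38 patients remain. Power is then 65.6 %, so imbalance of this size changes little beyond the overall loss.

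**The case against.** The strongest reply is that the direction of the error is not known. The article gives no inflation formula, and 128 × 1.5 is 192, not 190, so the mechanism is inferred. The authors may have meant a 50 % mark-up on 128, which corresponds to a loss of about one third. In that case the wording of the loss is wrong, 190 is about right, and power is close to 80 %. This stands as an explanation. It does not remove the need for a correction, because the article describes the 50 % as loss to follow-up.

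A second reply is that the 67 % applies to an unadjusted completer comparison, while the analysis model may be set out in a document not shown. The section Data analysis says only that outcomes are compared between the groups at 3 and 6 months. Adjustment for baseline MARS-D could recover some power. With 95 completers it would be about 71 % at a baseline-to-6-month correlation of 0.3, 75 % at 0.4, 80 % at 0.5 and 85 % at 0.6. The article gives no such correlation, so these values are only illustrative. This point also stands as a qualification: 67 % describes the test behind the sample size, not necessarily the final analysis. But the stated 80 % was derived without adjustment, so it cannot be rescued by an adjustment that the calculation does not use.

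Other readings do not help. The word for approximately before the 50 % does not stretch to 33 %, and every loss from 40 % to 55 % falls short of 80 % power. A one-sided test with 95 completers would give about 78 to 79 %, still below 80 %, and it would not reproduce 128.

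**Conclusion.** The concern holds. The figures 128, about 50 % and 190 are inconsistent, and nothing else in the article reconciles them. This conclusion needs no assumption about how 190 was reached.

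Taken at its word, the plan expects 95 patients in the primary comparison and has 67.4 % power for the 4-point difference, against the stated 80 %. The chance of missing that effect rises from 20 % to about 33 %. The power figure rests on a true loss of 50 %, a two-sided 5 % t-test, equal arms and an unadjusted comparison of completers. If the intended loss was about one third, the power statement survives and the loss figure is the error. The sentence must be corrected in either case.

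**What to change.** The sponsor should state which of the figures was intended and correct the sentence accordingly:

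- **If 50 % is the expected loss and enrolment stays at 190:** say that 95 participants are expected to be analysed, which gives about 67 % power for a 4-point difference with SD 8, and that 80 % power is reached only if the loss does not exceed about 33 %.
- **If a loss of about one third was meant:** replace 50 % with that figure. 190 enrolled and 80 % power then agree.
- **If both 50 % loss and 80 % power are to be kept:** enrolment has to be 256, which is 66 more patients.

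The first two options cost one corrected sentence and no extra patients. The first also makes the stated power less favourable. If the sponsor relies on baseline adjustment to make up part of the shortfall, the sample-size section should say so and give the assumed correlation.

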### Recruitment and participants

Patients are recruited from three psychiatric hospitals in the region shortly before their discharge. The inclusion criteria are met if the patient is at least 18 years old, has a medical diagnosis in the field of bipolar disorders (ICD-10 F31), schizoaffective disorders (ICD-10 F25) or any form of schizophrenia (ICD-10 F20). Patients with already scheduled inpatient treatments within the next 6 months are excluded. In addition, patients can’t participate, if they are not reachable by phone. The study psychologist visits the participating hospital departments to inform the patients on site and invite them to participate in the study. All patients have to give written informed consent. Therein the patients declare consent tobe contacted by the study nurse over a period of 6 months by call and by text messagesto the scientific evaluation of the collected data in a pseudonymised formto be possibly contacted again after the participation in the project to ascertain how further treatment is progressingthe use of further data (like data from hospital information systems about other in- or outpatient treatments or data of the statutory health insurance) in the evaluation.

Patients can withdraw their consent or parts of it anytime and without giving reasons. The withdrawal does not create disadvantages.

The recruitment phase of the project started February 2015.

### Baseline and follow-up interviews

Shortly before their discharge from the hospital, all participants receive a baseline interview conducted on site by the study psychologist. The baseline interview consists of the assessment of personal data (name, address, telephone number, date of birth), diagnoses, medication, by the patients’ desired topics for the telephone calls and several standardized questionnaires covering the outcomes of the study. The diagnoses are taken from the medical record. In addition the Structured Clinical Interview for DSM-IV (SCID I) is performed, but only the specific sections about affective disorders and the sections about the psychotic disorders [29]. Topics for telephone calls selected from a list by the patient are medication, housing/living, work, finances, spare time, friends, family, partnership, everyday life, diseases and others.

The medication adherence is measured using the Medication Adherence Report Scale, German version (MARS-D) [30]. The MARS-D consists of five items, detecting non-adherent behaviour by self-report. It is known that patients tend to overestimate their adherence [31–33] or to conceal non-adherent behaviour [30]. The MARS-5 (original Medication Adherence Report Scale in English language) was developed to take the frequency of non-adherent behaviour into account and to encourage the patient to answer truthfully to the questions that are asked in a non-threatening and non-judgmental way to minimize social desirability bias [34, 35].

The mental health status is measured by the Brief Psychiatric Rating Scale (BPRS). This instrument consists of 18 items to measure the severity of psychiatric symptoms [36, 37]. The Young Mania Rating Scale (YMRS) in German Language will be used for the assessment and quantification of manic symptoms [38].

Quality of life will be measured on the basis of the short version of the subjective instrument World Health Organization Quality of Life (WHOQOL-BREF), which is designed for generic use [39, 40].

The psychological, social and occupational function levels will be assessed by the Global Assessment of Functioning (GAF) on a scale from 1 to 100, intended as a hypothetical continuum of mental health (score 91–100) to illness (score 1–10) [41].

In the baseline interview the following issues will also be assessed in a standardized computer assisted personal interview:Socio-demographic informationSide effects of medication according to a list of common side effects of psychotropic drugsSocial support (F-SozU, short form with 14 items) [42]Short scale social desirability-gamma (KSE-G) [43]Resilience scale (RS-11, short form with 11 items) [44]Use of alcohol, drugs and smoking status [45, 46]Childhood Trauma Questionnaire (CTQ) [47]

The 3- and 6-months-follow-ups will be conducted by telephone by the nurses of the telemedicine centre as a computer assisted personal interview. In both follow-ups, the MARS-D, WHOQOL-BREF, the side effects of medication, social support, social desirability, the resilience scale and furthermore, changes in medication and the utilization of in- and outpatient treatment will be assessed. The utilization of other treatments will be assessed by asking whether the participants have visited a general practitioner or other specialized physicians including psychotherapist/psychiatrists within the last three respectively 6 months and if so, how often. Also the number and duration of hospital stays are questioned. The GAF will be assessed only in the 6-months-follow-up.

In the 6-months-follow-up the participants in the intervention group will also be asked how they evaluate the intervention (Table 1).

**Table 1 Tab1:** Interview questions and answers to assess acceptance and satisfaction of the participants

Question:	How would you assess the telephone and text messages contacts during the last 6 months?
Answer:	Very helpful – little helpful – not helpful – other (free text) – don’t know – no answer
Question:	Could you imagine continuing the telephone contacts in this form?
Answer:	Yes – No – don’t know – no answer
Question:	Do you think this kind of care can partly replace personal contacts with physicians or psychologists?
Answer:	Yes – No – don’t know – no answer
Question:	Is there something you would change or improve?
Answer:	Yes – No – don’t know – no answer and additional free text

